#### Dose escalation scheme

As long as no DLE is observed, a classic three-at-one design will be followed [22]. After the first DLE is observed one more patient will be recruited at the same dose before the dose will be determined as the maximum tolerated dose following the model outlined above. The highest dose with a median probability of tolerability being at least 33 per cent will be applied as the current MTD to the subsequent patient, following the Continual Reassessment Method [23]. If the MTD is ever to be calculated as being "dose 0", the trial ends prematurely at any time with the result that no safe dose could be established (Figure 2). Nine consecutive patients will be allocated to Group 1 before nine more patients will be allocated to Group 2. As the metaparameters α and β are assumed to be correlated between groups, results from group 1 affect the escalation scheme in group 2.

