### Objectives

#### Primary objectives

The primary objective of the trial is related to the safety and tolerability of the Investigational Medicinal Product (IMP). The particular parameters for this objective are:

• Local and systemic safety and tolerability of intratumoral/intracerebral and intravenous/intracerebral administration of the IMP,

• Maximum tolerated dose (MTD) of the IMP as assessed by NCI CTCAE v4.0,

• Viremia following intratumoral, intracerebral and intravenous administration of the IMP,

• IMP shedding/persistence following intratumoral, intracerebral and intravenous administration of the IMP.

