**Figure 1 F1:**
[figure not shown]
**Schematic diagram of the ParvOryx01 trial: study group 1 will be treated first**. After completion of group 1 an interim analysis will be performed prior to recruiting patients for study group 2. Information about dose escalation is specified in Table 1.

**Table 1 T1:** Dose schedule for both study groups

GROUP I			
Escalation Level	Study Time	Dose and route of administration	Duration
**Level 1** Total dose: 1 × 10^6 ^pfu	Day 1	5 × 10^5 ^pfu, intratumoral (via catheter)	15 minutes
	
	Day 10	5 × 10^5 ^pfu, intracerebal (direct injection at multiple locations of resection wall)	15-30 minutes

**Level 2** Total dose: 5 × 10^7 ^pfu	Day 1	2.5 × 10^7 ^pfu, intratumoral (via catheter)	15 minutes
	
	Day 10	2.5 × 10^7 ^pfu, intracerebal (direct injection at multiple locations of resection wall)	15-30 minutes

**Level 3** Total dose: 1 × 10^9 ^pfu	Day 1	5 × 10^8 ^pfu, intratumoral (via catheter)	15 minutes
	
	Day 10	5 × 10^8 ^pfu, intracerebral (direct injection at multiple locations of resection wall)	15-30 minutes

GROUP II			
**Escalation Level**	**Study Time**	**Dose and Route of Administration**	**Duration**

**Level 1 **Total dose: 1 × 10^6 ^pfu	Day 1 - 5	1 × 10^5 ^pfu, intravenous infusion	2 hours
	
	Day 10	5 × 10^5 ^pfu, intracerebral (direct injection at multiple locations of resection wall)	15-30 minutes

**Level 2** Total dose: 5 × 10^7^	Day 1 - 5	0.5 × 10^7 ^pfu, intravenous infusion	2 hours
	
	Day 10	2.5 × 10^7 ^pfu, intracerebral (direct injection at multiple locations of resection wall)	15-30 minutes

**Level 3 **Total dose: 1 × 10^9 ^pfu	Day 1 - 5	1 × 10^8 ^pfu, intravenous infusion	2 hours
	
	Day 10	5 × 10^8 ^pfu, intracerebral (direct injection at multiple locations of resection wall)	15-30 minutes

Specification of virus application and dose escalation during the Parvoryx01 trial: dose group 2 will be treated after completion of group 1 and after interim analysis of safety and tolerability in group 1.

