### Benefit/risk assessment

Currently, recurrent glioblastoma is a tumor entity for which no established standard of care exists. The prognosis of this disease is dismal, the progression free survival at 6 months (6 M-PFS) ranges between 15% to 21% and the median survival of patients is in the range of 25 weeks [19]. Re-operation is one possible treatment option with proven clinical benefit. It can be estimated that one third of patients with recurrent GBM are candidates for a second debulking surgical procedure.

Non-surgical treatment options include the application of re-irradiation for a subset of approximately 20% of patients and the use of chemotherapy. None of these treatments has been shown to have a major impact on PFS or survival.

The use of replication competent Parvovirus H-1 in the current trial setting therefore addresses a patient population without a standard of care and with only limited treatment options. According to the study protocol even without oncolytic efficacy of H-1PV patients would benefit from participating in the trial due to re-operation after initial virus treatment.

There is only limited information about the effects of Parvovirus H-1 infections of humans, but according to the assessment of the pathogenicity of the virus in humans by the Robert Koch Institut it is classified as non-pathogenic in man. This is supported by the limited available information from human patients. According to data from Parvovirus H-1 application in terminally ill tumor patients in 1965 and in 1993 the injection(s) did not cause severe side effects. The virus that was used in these patients (n = 2 in 1965 and n = 12 in 1993) was not produced according to today's GMP standard and the amount of virus that was injected was in the range from approx. 2 × 10 exp8 to approx. 3 × 10 exp10 [20,21]. Recently, it could also be demonstrated that even laboratory staff who had worked with Parvovirus H-1 for several years was tested negative for Parvovirus H-1 specific antibodies, ruling out active infection and pointing to a very low level of contagiousness of H-1PV in humans ([name], German Cancer Research Center (DKFZ), personal communication).

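### The MTD rules always name one of the three studied levels (or dose 0), so a group that meets no toxicity limit would still report an MTD, and the two rules would name different levels

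*Protocol article*

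**What the plan says.** Primary objectives lists "Maximum tolerated dose (MTD) of the IMP as assessed by NCI CTCAE v4.0" among the parameters of the primary objective, and the abstract also promises to determine the MTD.

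Two places say how the MTD is found:

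- **Analysis variables** calls a dose tolerable if its probability of a DLE is below 33%. It defines the MTD as the level whose posterior probability of toxicity at or below 33% is the largest. The answer is always one of the listed levels.
- **Dose escalation scheme** says: "The highest dose with a median probability of tolerability being at least 33 per cent will be applied as the current MTD", and gives that dose to the next patient. The only other outcome is dose 0, at which the trial ends with no safe dose established.

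Table 1 stops at level 3 in both groups: "Total dose: 1 × 10^9 ^pfu". Benefit/risk assessment reports 14 earlier patients (2 + 12) in whom "the injection(s) did not cause severe side effects" and "the amount of virus that was injected was in the range from approx. 2 × 10 exp8 to approx. 3 × 10 exp10". It adds that this virus was not made to the present GMP standard, and it gives no unit for the amounts. The same section takes the animal toxicology as support for a low risk of side effects.

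**The concern.** The scheme provides for toxicity that begins below the studied range (dose 0) but not for tolerability that extends to its top. If level 3 is well tolerated, no higher level has been studied and nothing bounds the tolerable dose from above. The honest result is that the MTD was not reached, and the rules cannot return it.

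The label attaches to a primary result. A level named as MTD reads as a toxicity ceiling, and the Discussion expects the intravenous arm to inform later trials in non-CNS tumours. If the two rules also pick different levels from the same data, the reported MTD depends on which section the analyst follows.

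**Working it through.** **Inputs.** Three levels per group, nine patients per group, and three patients per level while no DLE occurs (Sample size; Dose escalation scheme). Model and prior from Statistical methods: the logits of toxicity at levels 1, 2 and 3 are a − b, a and a + b. In group 1, a and b are normal with mean 0, variance 4 each and covariance −0.2.

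**Dose totals reproduced.** Level 3, group 1: 5 × 10^8 + 5 × 10^8 = 1 × 10^9 pfu. Level 3, group 2: 5 × (1 × 10^8) + 5 × 10^8 = 1 × 10^9 pfu. Both match Table 1.

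**Check of the model set-up, before any data.** The prior variances of the logits are 4 + 4 + 2(0.2) = 8.4, 4, and 4 + 4 − 2(0.2) = 7.6. With ln(0.33/0.67) = −0.708, the prior P(toxicity ≤ 33%) is Φ(−0.708/√8.4), Φ(−0.708/√4) and Φ(−0.708/√7.6), that is about 0.40, 0.36 and 0.40. Simulation from the prior gives 0.404, 0.362 and 0.399, which agrees.

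**Posterior.** The likelihood multiplies the prior by p^x (1 − p)^(n − x) at each level, where x is the number of DLEs among n patients. For group 1 data alone:

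| Outcome | Quantity | Level 1 | Level 2 | Level 3 |
|---|---|---|---|---|
| 0 DLE in 9 (3/3/3) | P(toxicity ≤ 33%) | 0.941 | 0.993 | 0.935 |
| | median toxicity | 0.046 | 0.046 | 0.053 |
| | 95th percentile | 0.35 | 0.20 | 0.37 |
| 1 DLE in 3 at level 3, none below | P(toxicity ≤ 33%) | 0.962 | 0.953 | 0.583 |
| | median toxicity | 0.03 | 0.10 | 0.28 |

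**Applying the rules to 0 DLE in 9.**

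- Analysis variables takes the largest probability, 0.993, and names **level 2**. The middle level gains information from both neighbours and has the tightest posterior. It wins on precision, not because level 3 looked toxic.
- Dose escalation scheme takes the highest level that passes and names **level 3**. Level 3 passes whether its 33% is read as a toxicity limit (median 0.053) or literally as tolerability (1 − 0.053 = 0.947).
- Neither is an MTD in the ordinary sense, because no studied level was judged intolerable.

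**With one DLE at level 3**, its median toxicity of 0.28 is still below 33%, so the escalation rule again names level 3. The Analysis variables definition now names level 1.

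**With 0 DLE in all 18 patients**, P(toxicity ≤ 33%) is about 0.96, 1.00 and 0.96 in both groups, and the conclusions are the same.

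**How often could this arise?** The documents give no expected DLE rate. Assuming a rate r that is constant over levels, P(no DLE in 9) = (1 − r)^9:

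- r = 2%: 0.98^9 = 83%
- r = 5%: 0.95^9 = 63%
- r = 10%: 0.90^9 = 39%

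**The case against.** **The quoted sentence allocates the next patient; it is not the final reporting rule.** This is largely right. Giving the top level while it appears tolerable is normal conduct for the Continual Reassessment Method. A reader might infer that a well-tolerated level 3 would simply be reported as the MTD. That does not follow, because the formal definition in Analysis variables returns level 2 on the same data. The gap remains, since that definition has no outcome for an unreached MTD either.

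**The model may not operate when no DLE occurs.** Dose escalation scheme brings in the model after the first DLE. Statistical methods, however, has the posterior calculated whenever a subject enters, and the MTD definition carries no exception for groups without a DLE. The text is mixed on this, which is a further reason to state the final rule once.

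**The historical comparison is weak.** A reader might infer that the top dose lies 30-fold below amounts known to be safe in humans (3 × 10^10 / 1 × 10^9 = 30). The documents do not support that. Thirty is the upper end only; level 3 lies inside the earlier range, at five times its lower end (1 × 10^9 / 2 × 10^8). The unit is not stated and the material was not GMP grade. Absence of severe side effects is also not absence of DLEs, whose definition stands in the full protocol.

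**Three DLE-free patients at level 3 say little.** Taken alone they leave a one-sided 95% upper limit of 1 − 0.05^(1/3) = 63%. That ignores the protocol's model, whose 95th posterior percentile is about 37%, so the 63% should not be pressed.

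**Reporting labels belong in the full protocol or SAP.** This would answer a mere omission. Here the article does state the definition, and the definition forces a listed level.

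**Conclusion.** The concern holds in this form: as written, the rules must return one of three levels or dose 0, so they can name an MTD when no toxicity limit has been met. They also disagree about which level that is: level 2 against level 3 with no DLE in nine patients, and level 1 against level 3 with one DLE at the top level.

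That result rests only on the stated model, prior and rules. How likely the scenario is rests on assumed DLE rates and on the protocol's own expectation of low risk, which makes few or no DLEs plausible but not established. The earlier human amounts include the level 3 dose and extend above it; they add context, and the defect does not depend on them. Nothing here shows that the dose range is wrong or that stopping at level 3 is illegitimate. The problem is what the trial may claim from it, and it should be corrected.

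**What to change.** 1. Reconcile Analysis variables and Dose escalation scheme into one rule for the final MTD, stated separately from the rule that allocates the next patient. This must come first: a trigger based on level 3 being the selected dose would not fire under the present definition, which selects level 2 when no DLE occurs.
2. Add the upper counterpart of dose 0. If the highest studied level meets the tolerability criterion at the end of a group, report that the MTD was not reached within the range studied, the highest administered dose, and the model's posterior interval for its DLE rate.
3. Report an MTD only if a higher studied level is judged not tolerable.
4. Align the abstract and Primary objectives: determine the MTD or, if it is not reached, the highest administered dose within the range studied.

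No dose level, schedule or patient number changes. The cost is a few sentences and a weaker headline claim when no toxicity is seen.

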### Statistical analysis

#### Analysis variables

The primary criterion for dose modification is the relative frequency of a dose-limiting event (DLE) at a given dose level. Toxicity of a dose is defined as the probability of this dose being associated with a DLE in a patient as indicated in the trial protocol. A dose is defined as tolerable if the probability of toxicity is lower than 33 per cent. The maximum tolerated dose is defined as the dose level with the highest posterior probability of having a toxicity not higher than 33 per cent.

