#### Statistical methods

The posterior probability for toxicity will be calculated in a logistic model, where the toxicities are parametrized as follows: *p_ij_*: toxicity for group i, level j, $\text{log}\left(p_{i1}/\left(1-p_{i1}\right)\right)=a_{i}-\beta_{i;}\text{log}\left(p_{i2}/\left(1-p_{i2}\right)\right)=a_{i}\text{log}\left(p_{i3}/\left(1-p_{i3}\right)\right)=a_{i}+\beta_{i};$ with the following prior distribution for the intercept and slope parameters:

$$\left(\alpha_{1},\beta_{1},\alpha_{2},\beta_{2}\right)\sim N\left(\left(\begin{array}{c} 0\\ 0\\ 0\\ 0 \end{array}\right),\left(\begin{array}{cccc} 4 & -.2 & 1.6 & 0\\ -.2 & 4 & 0 & 1.6\\ 1.6 & 0 & 4 & -.2\\ 0 & 1.6 & -.2 & 4 \end{array}\right)\right)$$

Whenever a subject enters the study, the dose level will be elicited by calculating the posterior probability for each dose level to be tolerable. The highest dose level that is tolerable will be allocated.

The following measurements will be subject to descriptive statistical methods: vital signs, serum levels and hematology data, H-1 PV specific antibodies, virus shedding. Progression Free Survival and Overall Survival will be listed per group and subject, showing observation time and event status.

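### The dose-allocation sentence sets 33% as a floor on tolerability, while the plan's own definition sets 33% as a ceiling on toxicity, and no reading of the sentence reproduces that ceiling

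*Protocol article*

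**What the plan says.** Three sections of the protocol article bear on this.

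- **Analysis variables** defines the quantity and the limit: "Toxicity of a dose is defined as the probability of this dose being associated with a DLE in a patient", and "A dose is defined as tolerable if the probability of toxicity is lower than 33 per cent". It then defines the MTD as the "dose level with the highest posterior probability of having a toxicity not higher than 33 per cent".
- **Statistical methods** gives a logistic model for the three levels of each group and a normal prior. Dose assignment rests on "calculating the posterior probability for each dose level to be tolerable", followed by: "The highest dose level that is tolerable will be allocated". No cut-off for that posterior probability is given.
- **Dose escalation scheme** keeps to three patients per level until a DLE occurs. Then "After the first DLE is observed one more patient will be recruited at the same dose", and from there the model governs: "The highest dose with a median probability of tolerability being at least 33 per cent will be applied as the current MTD". If the model returns dose 0, the trial ends.

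The last sentence is the only numerical allocation cut-off in the article.

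**The concern.** The same 33% appears on opposite sides. Under Analysis variables it is the most toxicity a tolerable dose may have. Under Dose escalation scheme it is the least tolerability that qualifies a dose. The complement of toxicity below 33% is tolerability above 67%, so the two statements differ by about a factor of two in accepted toxicity.

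This is a first-in-man trial with the MTD among its primary objectives. The sentence decides the dose of every patient after the first DLE and the one that follows it, and it decides when the trial stops at dose 0. Group 1 results also feed the group 2 allocation through the correlated prior.

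**Working it through.** **Step 1: compare the limits.** Write p for the DLE probability at a dose.

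- Definition: tolerable if p < 0.33, that is 1 − p > 0.67.
- Reading 1 of the allocation sentence (tolerability = 1 − p): median(1 − p) ≥ 0.33, that is median p ≤ 1 − 0.33 = 0.67.
- Reading 2 (tolerability = posterior probability that p < 0.33): P(p < 0.33) ≥ 0.33, so P(p ≥ 0.33) may reach 0.67. The odds are 0.67/0.33, about 2 to 1 against the dose being tolerable.
- Yardstick, used only for comparison: the 33% ceiling applied to the posterior median, median p ≤ 0.33. This is the same as median tolerability ≥ 0.67 or P(p ≤ 0.33) ≥ 0.50.

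Neither reading equals the yardstick. Reading 1 fits the word median better; reading 2 fits the wording of Statistical methods better.

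**Step 2: compute posteriors for group 1.** The inputs from Statistical methods are logit p = α − β, α and α + β at levels 1, 2 and 3, with (α, β) normal, means 0, variances 4 and covariance −0.2. Posteriors were obtained on a numerical grid.

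| DLEs so far | Median toxicity at the level named | Yardstick | Reading 1 | Reading 2 |
|---|---|---|---|---|
| L1 0/3, L2 2/2 | L2: about 0.64 | level 1 | level 2 | level 1 |
| L1 0/3, L2 2/4 | L2: about 0.39 | level 1 | level 2 | level 2 |
| L1 0/3, L2 0/3, L3 2/3 | L3: about 0.58 | level 2 | level 3 | level 2 |
| L1 2/2 | L1: about 0.92; L3: 0.50 | dose 0 | level 3 | level 3 |

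The last row can be checked by hand. Cov(α − β, α + β) = 4 − 4 = 0, so level 1 data leave the level 3 distribution at its prior. The median stays at 0.50, so reading 1 admits level 3 (0.50 ≥ 0.33). Var(α + β) = 4 + 4 − 0.4 = 7.6 and logit(0.33) = −0.708, so P(p < 0.33) = Φ(−0.708/√7.6) = Φ(−0.257), about 0.40. Reading 2 admits it too.

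**Step 3: enumerate every nine-patient path in group 1.** The scheme is three per level until the first DLE, one more patient at that level, then the rule. The true DLE rates are assumptions; the article gives none. Dose 0 is counted whenever it is reached, including after the ninth patient.

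| Assumed true rates (levels 1/2/3) | Quantity | Yardstick | Reading 1 | Reading 2 |
|---|---|---|---|---|
| 10/20/40% | expected DLEs | 1.4 | 2.0 | 1.8 |
| 10/20/40% | expected patients at level 3 | 1.1 | 2.8 | 2.3 |
| 10/20/40% | dose 0 stop | 21% | 0.5% | 10% |
| 20/40/60% | expected DLEs | 1.8 | 3.3 | 2.5 |
| 20/40/60% | dose 0 stop | 46% | 4% | 29% |
| 60/65/70% | expected DLEs | 1.8 | 4.4 | 3.0 |
| 60/65/70% | dose 0 stop | 97% | 49% | 90% |

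Part of the difference in DLEs arises because the yardstick stops earlier and treats fewer patients. At 20/40/60% it treats 4.03 + 1.97 + 0.34 = 6.34 patients on average, against 8.81 and 7.69. DLEs per treated patient are 1.80/6.34 = 0.28, 3.26/8.81 = 0.37 and 2.53/7.69 = 0.33, so a difference remains.

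**Step 4: the separate MTD definition.** Analysis variables picks the level with the highest P(p ≤ 0.33), not the highest level that passes a cut-off. In the first three rows of the Step 2 table it picks level 1, whereas the allocation rules give levels 1 to 3.

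**The case against.** Several points on the other side have weight.

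- **It may be a verbal slip**, tolerability written for toxicity. Figure 2 holds the group 1 decision tree and may follow the 33% toxicity limit, but it is not available here. This stands as a limit on what can be said about the doses patients would actually be given. It does not make the sentence right.
- **Human oversight.** Trial schedule and duration requires agreement of investigator and sponsor before the second and third subject of a level, and DSMB consent before the next level. That reduces the risk, but it does not settle which threshold the model applies.
- **Final MTD.** A reader might infer that the rule would usually declare level 3 as the MTD. The article does not support this. The allocation sentence concerns the current MTD for the next patient, and Analysis variables defines the MTD differently. With that definition applied at the end of the same paths (rates 10/20/40%), level 3 is declared in 0%, 7% and 5% of runs (yardstick, reading 1, reading 2).
- **The dose 0 stop.** A reader might infer that it is close to disabled. That holds only for reading 1 at low to moderate rates. Under reading 2 it is weakened but still works, and at 60/65/70% even reading 1 stops in 49% of runs.
- **The start of the trial.** With a prior median of 50% at every level, both readings would admit level 3 before any data. This has no effect, because the three-per-level scheme governs until the first DLE.
- **The yardstick has its own cost.** It stops group 1 in 21% of runs at 10/20/40%, where levels 1 and 2 both meet the plan's limit. One DLE in two patients at level 1 is enough to trigger it.

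**Conclusion.** The contradiction is real and should be corrected before the rule is used. The article gives a ceiling of 33% on toxicity and an allocation floor of 33% on tolerability, and no text shown reconciles them. Literally read, the rule accepts either a posterior median toxicity of up to 67% or a 2 to 1 chance that the dose is intolerable. The 67% is a posterior quantity, not a bound on true toxicity.

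The supportable consequence is exposure after the first DLE. At assumed rates of 10/20/40% it is about 0.4 to 0.6 additional expected DLEs in group 1 (1.8 − 1.4 and 2.0 − 1.4), 1.2 to 1.7 more patients at level 3 (2.3 − 1.1 and 2.8 − 1.1), and a dose 0 stop that falls from 21% to 10% or 0.5%. These figures rest on assumed true rates, cover group 1 only, follow the model without oversight decisions, and use a median-based yardstick that Analysis variables does not itself state. Confidence is high for the conflict of wording and lower for what patients would receive.

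**What to change.** Reconcile Analysis variables, Statistical methods and Dose escalation scheme so that the 33% refers to one named quantity in one direction. It should be clear whether that quantity is the posterior median of the DLE probability or the posterior probability of being tolerable, with its cut-off. State which criterion governs each of three decisions: the next patient's dose, the dose 0 stop and the final MTD. If the final MTD is meant to follow a different rule from allocation, say so. Check every branch of Figure 2 against the stated criterion.

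Then report operating characteristics under a range of assumed DLE rates, including the chance of stopping early, since the candidate criteria differ widely on that. Which limit and stopping rule are clinically right is for the sponsor and the DSMB to decide.

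The text change is small. The enumeration of group 1 is quick to run. The real cost is the decision itself, because choosing a criterion changes how often the trial stops and how many patients reach the higher levels.

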### Sample size

The current trial represents the first in man study with the IMP (ParvOryx). 18 subjects will be allocated to 2 study groups with 9 subjects per group. Per group, 3 dose levels will be investigated. The mean number of 3 subjects per dose level appears to be sufficient to give first indications about safety, tolerability and proof of concept of ParvOryx.

There will be no a-priori defined quantitative ratio between females and males. However, no gender differences in the safety, tolerability as well as efficacy are expected on the basis of preclinical findings.

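### The dose-finding prior (all means 0, slope unrestricted) does not fit the 33% tolerability limit, and three sections word the decision rule differently; depending on the reading, group 1 stops too readily or level 3 is selected after two DLEs at level 1

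*Protocol article*

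**What the plan says.** All places are in the protocol article.

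- **Analysis variables.** "A dose is defined as tolerable if the probability of toxicity is lower than 33 per cent". The MTD rule is as follows: "The maximum tolerated dose is defined as the dose level with the highest posterior probability of having a toxicity not higher than 33 per cent", which is an argmax.
- **Statistical methods.** The model is logistic: logit toxicity is α − β at level 1, α at level 2 and α + β at level 3. It is given "with the following prior distribution for the intercept and slope parameters". All four means are 0, all variances are 4, the within-group covariance of α and β is −0.2, and the same parameter has covariance 1.6 across groups. No sign restriction on β is printed. Allocation: "The highest dose level that is tolerable will be allocated", with no cut-off for the posterior probability.
- **Dose escalation scheme.** A three-at-one lead-in runs until the first DLE. One more patient is then treated at that dose, and only after that does the model decide. The dose given is the highest whose median probability of tolerability reaches 33%. On dose 0, "the trial ends prematurely at any time with the result that no safe dose could be established". The text does not say how dose 0 is calculated; Figure 2 maps the paths for group 1.

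**The concern.** A prior for a dose-finding model should agree with the criterion it feeds, and with the idea that a higher level is not safer than a lower one. This prior does neither. Every level starts with median toxicity 0.50 against a limit of 0.33. Because β may be negative, the model can treat level 3 as safer than level 1.

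With at most nine patients per group, the prior carries much of the weight in the first model-based decision. That decision can end the trial for both routes, since group 2 follows group 1, or it can pick the next level. Because three sections state the rule differently, the same data lead either to dose 0 or to level 3, whose total dose in Table 1 is 1000 times that of level 1.

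**Working it through.** The text gives no operating figure to reproduce. The inputs are the printed prior (matrix read as a covariance matrix), the 0.33 limit, the lead-in and nine patients in group 1.

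**Prior.** logit(0.33) = ln(0.33/0.67) = −0.708.
- Var(α − β) = 4 + 4 + 0.4 = 8.4, sd 2.90; Var(α) = 4, sd 2.00; Var(α + β) = 4 + 4 − 0.4 = 7.6, sd 2.76.
- All logit means are 0, so every median toxicity is 0.50. P(tolerable) = Φ(−0.708/sd) = 0.40, 0.36, 0.40.
- Cov(α − β, α + β) = 4 − 4 = 0. The logits are jointly normal, so levels 1 and 3 are independent a priori, and level 1 data leave level 3 unchanged.

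**Posterior after level 1 data in group 1** (numerical integration; levels 1/2/3):

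| DLEs/patients at level 1 | Median toxicity | P(tolerable) |
|---|---|---|
| 1/2 | 0.50 / 0.50 / 0.50 | 0.30 / 0.32 / 0.40 |
| 2/2 | 0.92 / 0.78 / 0.50 | 0.02 / 0.11 / 0.40 |
| 1/3 | 0.334 / 0.41 / 0.50 | 0.49 / 0.41 / 0.40 |
| 1/4 | 0.25 / 0.36 / 0.50 | 0.64 / 0.47 / 0.40 |

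The 1/2 row is exact by symmetry: the likelihood p(1 − p) and the prior are both unchanged when (α, β) becomes (−α, −β).

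**What each reading decides**
- *Median toxicity at most 33%.* This is the same as P(tolerable) at least 50%. Both 1/2 and 2/2 give dose 0. 1/3 also gives dose 0, but only by 0.334 against 0.33. 1/4 continues at level 1.
- *P(tolerable) at least 33%.* 1/2 and 2/2 both select level 3 (0.40).
- *Argmax, as in Analysis variables.* 1/2 and 2/2 both select level 3. An argmax always names a level, so it can never return dose 0.
- *Median of (1 − p) at least 33%.* This accepts toxicity up to 67% and also selects level 3.

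**Operating characteristics of group 1** (enumeration of all paths)
- Median rule, true toxicity 10% at every level. First DLE in patient 1: 0.10. First DLE in patient 2: 0.9 × 0.1 = 0.09. First DLE in patient 3 and a DLE in patient 4: 0.81 × 0.1 × 0.1 = 0.008. These sum to 0.198, and later paths bring the probability of dose 0 to 20.8%. At 5% toxicity it is 10.2%.
- If the near-tie is counted as passing (cut-off 0.335), these become about 14% and 6%.
- P(tolerable) at least 33%: dose 0 in 2.5% of trials at 10% toxicity. With true toxicity 50/65/80%, about 89% of trials reach level 3.

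**Group 2 after a DLE-free group 1** (2 million draws). 1/2 at level 1 gives medians 0.425/0.308/0.216, so the median rule does not stop. 2/2 gives 0.86/0.57/0.21, so level 3 still passes that rule.

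**The case against.** A reader might infer that the plan rates every dose intolerable before any data, and that one DLE in the first patient certainly ends the trial. The documents do not support that:
- The stop follows from a median-toxicity rule that is not printed in those words. Under the wording in Dose escalation scheme, read as a probability of at least 33%, every level qualifies before data (0.40/0.36/0.40) and a first-patient DLE does not give dose 0.
- Figure 2 is not shown and may settle the rule.
- The pre-data rating has no effect by itself, because the lead-in runs without the model. The stop comes only after one further patient, and it concerns group 1, not group 2 after a DLE-free group 1.
- The stop after a first DLE in patient 2 is a near-tie.

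A reader might also infer that the prior contradicts Benefit/risk assessment, where earlier use is said to show that "the injection(s) did not cause severe side effects". That section also calls the human information limited, the virus then used was not GMP grade, and absence of severe side effects is not a DLE rate. A cautious prior in a first-in-man trial is a legitimate choice.

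Nor does "Per group, 3 dose levels will be investigated" in Sample size amount to a broken promise: Intervention makes each increase conditional on no dose-limiting events, and Trial schedule and duration requires DSMB consent before the next level. That consent is also a practical check on a jump to level 3.

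These points limit the claim. They do not rescue the prior, since the readings that avoid the early stop are those that send the next patient to level 3 after two DLEs in two patients at level 1. That fits poorly with the sequential escalation described under Design.

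**Conclusion.** The point holds in a conditional form. Independently of the reading, prior median toxicity is 0.50 at every level, level 1 results say nothing about level 3, and the three sections do not give one rule. The consequence depends on the reading:
- under posterior median toxicity at most 33%, group 1 ends with no safe dose in about 21% of trials at 10% true toxicity and 10% at 5% (about 14% and 6% if the near-tie passes);
- under P(tolerable) at least 33%, that happens in 2.5% at 10%, but level 3 is reached in about 89% of trials at 50/65/80% toxicity.

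These figures assume the printed prior with no restriction on β, the lead-in as described, allocation by the model alone (no DSMB intervention), and the stated true toxicities, which are illustrative and not taken from the document. Which consequence applies cannot be settled from the text. It should be corrected before the model is used.

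**What to change.** 1. Reconcile Analysis variables, Statistical methods and Dose escalation scheme into one decision rule that matches Figure 2 and says how dose 0 is calculated. Which rule is clinically right is for the sponsor and the DSMB.
2. Restrict the slope to be positive, and set the intercept prior together with that restriction so that the starting level meets the plan's own criterion before data. Neither step is enough alone:
   - with β > 0 and α mean still 0, level 1 starts at median 0.165, but one DLE in two patients gives 0.378, so the median rule still returns dose 0;
   - with α mean −1.5 and β unrestricted, two DLEs in two patients at level 1 leave the level 3 median at 0.18, and level 3 is reached in 88% of trials at 50/65/80% toxicity.
3. Report simulated operating characteristics for the chosen rule and prior: probability of dose 0, probability of reaching each level and expected patients per level.

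Illustration only, under the median rule: with α mean −1.5 and β > 0, dose 0 at 10% toxicity falls from 21% to 6%. The downside is real. At 50/65/80% toxicity, stops fall from about 92% to 84%, counting a dose 0 result after the ninth patient (90% to 81% counting only earlier stops). Failures to stop therefore roughly double, from about 8% to 16% (10% to 19%). The sponsor should weigh this openly in a first-in-man trial. The work itself is a prior change, a short simulation and a text revision.
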